### **12.3 Health economic evaluation**

The analysis will be performed using the CORE Diabetes Model (CDM; IMS Health, Basel, Switzerland). The CDM is a validated non-product-specific policy analysis tool for cost-effectiveness analysis in both type 1 and type 2 diabetes; a detailed description of the model architecture (including schematic diagrams) and validation is available in publications by Palmer et al (45; 46) and more recently McEwan et al (47). In summary, the model is based on a series of inter-dependent submodels that simulate both acute and long-term diabetes-related complications (angina, myocardial infarction, congestive heart failure, stroke, peripheral vascular disease, diabetic retinopathy, macula oedema, cataract, hypoglycaemia, ketoacidosis, lactic acidosis, depression, oedema, nephropathy and end-stage renal disease, neuropathy, foot ulcer and amputation, and non-specific mortality). The sub-models have a semi-Markov structure and use time, state, time-in-

state and diabetes type-dependent probabilities derived from published sources to simulate disease progression. Monte Carlo simulation using tracker variables is used to overcome the memory-less properties of the standard Markov model and allows for interconnectivity and interaction between individual sub-models.

### 12.3.1 Simulation cohort and treatment effects

Baseline characteristics of the simulation cohort will come from the trial. They will include: age, sex ratio, Hb1Ac and other risk factors. Treatment effects will be based on the trial findings at 12 months for both arms: closed loop versus MDI.

### 12.3.2 Costs and utilities

The base-case analysis will be performed from the perspective of the UK National Health Service. Direct costs will be sourced from published literature and where necessary inflated to the current year costs (48-59).

For treatment costs, only the incremental costs between the two arms will be considered, namely the difference between closed loop therapy versus MDI. Average UK costs for will be sourced from the British National Formulary 63.

Health state utility values will be taken from published literature (60) and references therein.

## 12.4 Laboratory methods

### 12.4.1 Screening and reference sample

Thyroid function (TSH, fT4) and anti-transglutaminase antibodies with IgA levels (to exclude diagnosis of coeliac disease) and full blood count will be measured locally if not already done during diagnosis.

### 12.4.2 Lipid profile

Venous blood samples for the measurement of total cholesterol, triglycerides, HDL, and LDL cholesterol will be taken at baseline, 12 months and 24 months post diagnosis, and will be measured locally.

For the extension phase, venous blood samples for the measurement of total cholesterol, triglycerides, HDL, and LDL cholesterol will be taken at 36 and 48 months post-diagnosis and will be measured locally.

### 12.4.3 C-peptide

Venous blood samples for the measurement of plasma C-peptide will be taken during Mixed Meal Tolerance Tests (MMTT) at baseline, 6 months, 12 months and 24 months post-diagnosis (see section 12.1.2). Plasma samples for C-peptide will be processed locally and stored deep frozen (-20°C or below) until analysis at a central laboratory.

For the extension phase, venous blood samples for the measurement of fasting plasma C-peptide will be taken at 36 and 48 months post-diagnosis. Plasma samples for C-peptide will be processed locally and stored deep frozen (-20°C or below) until analysis at a central laboratory.

### 12.4.4 Plasma glucose

Plasma samples for glucose will be taken during MMTT at baseline, 6 months, 12 months and 24 months post-diagnosis (see 9.3.1 and 12.1.2). Plasma samples for glucose will be processed locally and stored until analysis at a central laboratory.

For the extension phase, plasma samples for the measurement of fasting glucose will be taken at 36 and 48 months post-diagnosis. Plasma samples for glucose will be processed locally and stored until analysis at a central laboratory.

### 12.4.5 HbA1c

Blood samples for the measurement of HbA1c levels will be taken at baseline, at 3 monthly follow up visits, and at the end of the study.

For the extension phase, blood samples for the measurement of HbA1c levels will be taken at 36 and 48 months post-diagnosis.

HbA1c will be measured at a central laboratory using an International Federation of Clinical Chemistry and Laboratory Medicine (IFCC) aligned method. HbA1c testing will follow National Glycohemoglobin Standardization Program (NGSP) standards. A local laboratory/point-of-care backup measurement of HbA1c will be made.

### 12.4.6 Immunological assessment

If the treatment group achieves “metabolic rest” for the islet cell, it may dampen the immune response. During MMTT at baseline, 6 12 and 24 months, we will take and store blood/serum/plasma samples for a subsequent analysis to assess changes in immune markers in intensively treated participants as a result of decreased metabolic activity of their islet cells or a direct effect of improved glycaemic control. Immunological assessment may include analysis of peripheral blood mononuclear cells (PBMCs) and DNA.

## 12.5 Blood loss

| Test          | Source | Tube type    | Tube Volume ml | Visit 2 baseline | Visit 6 3 months | Visit 7 6 months | Visit 8 9 months | Visit 9 12 months | Visit 10 15 months | Visit 11 18 months | Visit 12 21 months | Visit 14 24 months | Visit 15 36 months | Visit 17 48 months |
|---------------|--------|--------------|----------------|------------------|------------------|------------------|------------------|-------------------|--------------------|--------------------|--------------------|--------------------|--------------------|--------------------|
| C-peptide     | Blood  | Lith Heparin | 1.2            | 7x
(8.4 ml)   |                  | 7x
(8.4 ml)   |                  | 7x
(8.4 ml)    |                    |                    |                    | 7x
(8.4 ml)     | 1x
(1.2 ml)     | 1x
(1.2ml)      |
| Glucose       | Blood  | Flouride     | 1.2            | 7x
(8.4 ml)   |                  | 7x
(8.4 ml)   |                  | 7x
(8.4 ml)    |                    |                    |                    | 7x
(8.4 ml)     | 1x
(1.2 ml)     | 1x
(1.2ml)      |
| Lipid profile | Blood  | Serum Gel    | 1.1            | 1x
(1.1 ml)   |                  |                  |                  | 1x
(1.1ml)     |                    |                    |                    | 1x
(1.1 ml)     | 1x
(1.1 ml)     | 1x
(1.1 ml)     |
| HbA1c         | Blood  | EDTA         | 1.2            | 1x
(1.2 ml)   | 1x
(1.2 ml)   | 1x
(1.2 ml)   | 1x
(1.2 ml)   | 1x
(1.2 ml)    | 1x
(1.2 ml)     | 1x
(1.2 ml)     | 1x
(1.2 ml)     | 1x
(1.2 ml)     | 1x
(1.2 ml)     | 1x
(1.2 ml)     |
| Immunology    | Blood  | Lith Heparin | 4.9/7.5        | 1x
(30 ml)    |                  | 1x
(20 ml)    |                  | 1x
(20 ml)     |                    |                    |                    | 1x
(20 ml)      |                    |                    |
| Immunology    | Blood  | Serum Gel    | 1.1            | 1x
(1.1ml)    |                  | 1x
(1.1ml)    |                  | 1x
(1.1ml)     |                    |                    |                    | 1x
(1.1ml)      |                    |                    |
|               |        |              |                | 50.2 ml          | 1.2 ml           | 40.2 ml          | 1.2 ml           | 40.2 ml           | 1.2 ml             | 1.2 ml             | 1.2 ml             | 40.2 ml            | 4.7 ml             | 4.7 ml             |

The total blood loss over two years will be approximately: 175.7 ml.

For the extension phase, the total blood loss over two years will be approximately: 9.4ml.

## 13 Study materials and products

### 13.1 Insulin

During run-in and control intervention, rapid acting insulin analogues (insulin aspart, insulin lispro, insulin glulisine or similar or ultra-rapid insulin analogue) and long acting insulin analogues (insulin glargine, insulin detemir or similar) will be delivered subcutaneously using an insulin pen injection device in accordance with manufacturer instructions for use.

During closed loop intervention, rapid acting insulin analogues (insulin aspart, insulin lispro, insulin glulisine or similar or ultra-rapid insulin analogue) will be administered via an insulin pump as described below (see 13.3).

### 13.2 Multiple daily insulin injections during run-in and control intervention

During run-in and control intervention when multiple daily injection therapy will be applied, insulin will be administered using CE-marked insulin pen devices as per usual clinical practice.

### 13.3 Insulin pump with pump suspend feature

During day and night automated closed loop glucose control combined with threshold based pump interruption, the next generation Medtronic subcutaneous insulin infusion pump Medtronic 640G (Medtronic Minimed, Northridge, CA, USA) will be used. Threshold-suspend or predictive low glucose suspend feature will be initially set to suspend insulin delivery at sensor glucose values of 3.3 mmol/l or higher, after which the setting could range from 3.3 to 5.0 mmol/l.

To download insulin pump data during closed loop intervention Medtronic CareLink® Therapy Management Software or similar will be used.

For the follow up closed-loop platform (CamAPS FX), the Dana insulin pump (SOOIL) will be used. Glooko/Diasend® software or similar will be used to download insulin pump data at regular intervals.

### 13.4 Continuous subcutaneous glucose monitor

#### 13.4.1 Blinded Continuous Subcutaneous Glucose Monitor

FreeStyle Libre Pro sensor (Abbott Diabetes Care, Alameda, CA) or similar blinded CGM devices will be used. Insertions will be done by the research team according to manufacturer's instruction. FreeStyle Libre Pro automatically stores up to 14 days' worth of glucose data and requires no calibration.

To download blinded sensor data during run-in, interventional and control periods, Abbott Diabetes Care proprietary software or similar will be used.

Subjects in the control intervention already using a FreeStyle Libre sensor can use their own sensor instead of the study blinded FreeStyle LibrePro sensor.

### **13.4.2 Real-time Continuous Subcutaneous Glucose Monitor**

The next generation Medtronic Enlite 3 family real-time sensor with Enliteserter (Medtronic Minimed, Northridge, CA, USA) will be used in the study. The sensor will be calibrated according to manufacturer's instructions with additional calibration checks in the morning and evening.

To download real-time sensor data during closed loop intervention Medtronic CareLink® Therapy Management Software or similar will be used.

For the follow up closed-loop platform (CamAPS FX), the Dexcom G6 real-time sensor with sensor applicator (Dexcom, Northridge, CA, USA) will be the study CGM. The sensor will be calibrated according to manufacturer's instructions.

### **13.5 CareLink USB link**

The Medtronic CareLink™ USB is indicated for use commercially by patients at home and for clinicians in a medical office setting as a means of facilitating communication between Medtronic diabetes therapy management devices that use Paradigm-compatible RF telemetry and a personal computer that uses data management application software. The CareLink USB device will enable data from study insulin pumps to be uploaded to CareLink Clinical.

### **13.6 Smartphone**

An Android smartphone hosting CamAPS FX App (see 4.6) will be used.

### **13.7 Bayer CONTOUR™ Next Link blood glucose meter**

A Bayer Contour Next Link RF enabled BG Meter (Study Meter) will be provided to study participants for use throughout the trial. During closed loop, the meter measures will be used to calibrate the study pump. The study pumps use the calibration point in the real-time algorithm which calculates the sensor glucose values that are displayed to the subject.

### **13.8 Computer-based algorithm**

The Cambridge closed loop controller has been used safely and effectively in the closed loop studies in both children and adults with T1D (**study REC Ref. 06/Q0108/350, REC Ref. 07/H0306/116, REC Ref. 08/H0304/75, REC Ref. 08/H0308/297, REC Ref. 09/H0306/44, REC Ref. 10/H0304/87, REC Ref. 12/EE/0155, REC Ref. 12/EE/0034, and REC Ref. 12/EE/0424**).

## 13.9 Actiwatch

An Actiwatch (Philips Respironics, Bend, Oregon, USA) will be used to measure sleep over 7 day periods at 6, 12, and 24 months during each intervention arm

## 14 Data analysis

Analyses of study data will be conducted to address the primary and secondary objectives of the trial. All randomised participants will be included in the analysis according to intention to treat principle.

### 14.1 Primary analysis

The primary analysis will evaluate between group differences in the levels of the mean area under the stimulated C-peptide curve of mixed meal glucose tolerance test conducted 12 months post diagnosis.

### 14.2 Secondary analysis

#### 14.2.1 Biochemical evaluation

Secondary endpoints include trends over time in mean stimulated C-peptide AUC, fasting C-peptide, HbA1c levels, percentage of patients in each group with HbA1c <7.5% , insulin dose (U/kg), change in BMI standard deviation scores, change in blood pressure, and change in lipid profile. Based on CGM glucose levels during periods of blinded CGM sensors wear, the between group differences of the following parameter will be assessed: AUC less than 3.9mmol/l and 3.5mmol/l, time spent below target glucose (<3.9 mmol/l), time spent above target glucose (>10.0 mmol/l), time spent within the target glucose range (3.0mmol/l – 10.0 mmol/l), average, standard deviation, and the coefficient of variation of glucose levels, the time with glucose levels < 3.5 mmol/l, 3.0 mmol/l and <2.8 mmol/l, the time with glucose levels in the significant hyperglycaemia (glucose levels > 16.7 mmol/l), total, basal and bolus insulin dose. Trends in CGM and insulin data collected within intervention arms will be evaluated on a 3-monthly basis and on a 12 monthly basis during the extension phase. CGM and insulin data collected during intervention arms will also be compared to pre-intervention baseline CGM readings.

#### 14.2.2 Safety evaluation

Safety data including severe hypoglycaemia events and ketone-positive hyperglycaemia will be tabulated for all subjects, including drop-outs and withdrawals, irrespective of whether CGM data are available and irrespective of whether closed loop was operational. For purposes of analysis, a severe hypoglycaemic event will be defined as an event requiring assistance of another person actively to administer carbohydrate, glucagon, or other resuscitative actions. These episodes may be associated with sufficient neuroglycopenia to induce seizure or coma. If plasma glucose

measurements are not available during such an event, neurological recovery attributable to the restoration of plasma glucose to normal is considered sufficient evidence that the event was induced by a low plasma glucose concentration.

## **14.2.3 Human factors evaluation**

### **14.2.3.1 Questionnaires**

Descriptive tabulations of questionnaires will be carried out, and scores will be calculated using provided scaling and scoring tools as appropriate.

### **14.2.3.2 Cognitive evaluation**

Change in cognitive test performance from baseline to follow-up will be assessed, as a function of group (intervention or control) and C-peptide level.

### **14.2.3.3 Qualitative interviews**

To maximise rigour at least two experienced qualitative researchers will be involved in data analysis. A thematic analysis will be undertaken by these individuals who will independently review data and write separate reports before attending regular meetings to compare their interpretations and reach agreement on recurrent themes and findings. Interviews will be read through repeatedly and cross-compared in order to identify issues and themes which cut across different people's accounts. A key aspect of the analysis will involve exploring the experiences and views of participants in the closed loop arm of the trial, to better understand the impact of using a closed loop on diabetes self-management practices and quality of life. Participants accounts of using the closed loop will also be compared with individuals experiences of using MDI to manage Type I Diabetes identified from previously published literature. A final coding frame, reflecting the initial research questions and emergent themes, will be developed once all data have been reviewed and consensus reached on key themes and findings. NVivo9, a qualitative software package, will be used to facilitate data coding/retrieval.

### **14.2.3.4 Quality of sleep assessment using Actiwatch**

Sleep will be automatically scored by Actiware software using previously described and validated algorithms. Sleep duration will be calculated as the sum of all epochs scored as sleep during the time in bed. Variability across nights in a participant's sleep duration will be summarised using the coefficient of variation. Sleep data will be averaged across nights in each participant for each study period.

### **14.2.3.5 Focus groups**

Transcripts of focus group discussions will be thematically analysed using QSR NVivo qualitative analysis software.

#### 14.2.4 Health economics assessment

For each simulation, a simulated cohort of 1,000 patients will be run through the model 1,000 times using first-order Monte Carlo simulation. Long-term outcomes will include total direct costs, life expectancy, quality-adjusted life expectancy and time to onset of complications. Future costs will be discounted at a rate of 3.5% per annum and clinical outcomes discounted at a rate of 1.5% per annum in line with NICE guidance on long-term conditions where treatment effects are sustained over a prolonged period of time (61), if still applicable by the time of analysis. The mean values from the simulation (a total of 1,000 mean values, each from a cohort of 1,000 patients run through the model) will then be used to generate scatterplots of incremental costs versus incremental effectiveness (quality-adjusted life years [QALYs]) for closed loop vs. MDI. Data from the scatterplot will then be used to generate a cost-effectiveness acceptability curve.

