#### *Sensitivity analysis*

In order to explore the robustness of the base-case findings and establish the key drivers of results, a series of one-way simulations will be performed on those parameters.

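### The cost-effectiveness acceptability curve is specified from first-order simulation alone, with no stated sampling of treatment effects, costs or utilities, so it does not represent decision uncertainty

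*Combined protocol and SAP*

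**What the plan says.** Protocol 14.2.4 (Health economics assessment) sets out the chain: "For each simulation, a simulated cohort of 1,000 patients will be run through the model 1,000 times using first-order Monte Carlo simulation". The means from these runs, "a total of 1,000 mean values, each from a cohort of 1,000 patients run through the model", are plotted as incremental cost against incremental QALYs, and then: "Data from the scatterplot will then be used to generate a cost-effectiveness acceptability curve".

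The inputs are described in protocol 12.3:

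- Effects (12.3.1): "Treatment effects will be based on the trial findings at 12 months for both arms: closed loop versus MDI". No standard error, covariance or bootstrap is mentioned.
- Utilities (12.3.2): "Health state utility values will be taken from published literature (60) and references therein". Costs likewise come from published sources. No distribution is given for either.
- Role of simulation in the model (12.3): "Monte Carlo simulation using tracker variables is used to overcome the memory-less properties of the standard Markov model". This describes following individual patients, not sampling parameters.

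The only sensitivity analysis, at the end of 14.2.4, is that "a series of one-way simulations will be performed on those parameters". The parameters meant are not named.

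Protocol 10.6 lists the outputs and no method for uncertainty. SAP section 1 says the health economic evaluation is done elsewhere and mentioned only briefly, and SAP 7.7 adds no method. Protocol 14.2.4 is therefore the governing text.

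**The concern.** An acceptability curve is read as the probability that a treatment is cost-effective at each willingness to pay, given what is known about the inputs. First-order simulation redraws patients for a given set of parameters. Averaging over a cohort of m patients leaves a spread equal to the patient-level SD divided by the square root of m. That measures how precisely the computer has evaluated the model. It carries no information on how precisely the trial, or the literature, has estimated what goes into the model.

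Protocol 5.2.5 gives the purpose as informing reimbursement decisions, and the curve is the only probability statement planned for that purpose. If parameter uncertainty is left out, the curve will usually be steeper than the evidence justifies, and a decision-maker would take simulation error for decision uncertainty.

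**Working it through.** **1. The plan's own figures.** Section 14.2.4 gives settings (1,000 patients, 1,000 runs) and no derived result, so there is no economic figure to reproduce. The only figures in the documents that bear on the precision of a trial effect are in protocol 14.7: effect 0.126, SD 0.18, 44 per group, 90% power, two-sided 0.05.

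- Transformed means: ln(1.37) = 0.315 and ln(1.555) = 0.441; difference 0.126.
- Normal approximation: 43 per group. Noncentral t: power 0.894 at 43 and 0.901 at 44. The stated 44 reproduces.

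**2. Design-stage precision of that effect.**

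- SE = 0.18 × √(2/44) = 0.0384.
- Relative SE = 0.0384 / 0.126 = 0.305, about 30%.

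This is for log(C-peptide AUC + 1). The documents do not say which 12-month effects drive the model, so 30% is an anchor and not an estimate of the model's input uncertainty.

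**3. Planned probability, one illustration (all economic inputs assumed).** Mean incremental net benefit 2,000 pounds; patient-level SD 40,000 pounds; patients drawn independently in the two arms; normal model.

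- Simulation SE = 40,000 × √(2/1,000) = 1,789.
- Planned probability = Φ(2,000 / 1,789) = Φ(1.118) = 0.87.

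**4. Adding a parameter SE p, with the mean held at 2,000.** Probability = Φ(2,000 / √(1,789² + p²)). The last column shows what p would imply if the trial effect, at 30.5% relative SE, were the only uncertain input, benefit were proportional to it and incremental cost were a fixed fraction c of expected benefit. Then p / 2,000 = 0.305 / (1 − c).

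| p (pounds) | Total SE | Probability | Implied c |
|---|---|---|---|
| 0 (as planned) | 1,789 | 0.87 | – |
| 600 | 1,887 | 0.86 | about 0 |
| 1,000 | 2,049 | 0.84 | 0.39 |
| 3,000 | 3,493 | 0.72 | 0.80 |
| 10,000 | 10,159 | 0.58 | 0.94 |

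The gap runs from about 1 to 29 percentage points. It is small when benefit far exceeds cost and large when the two are close.

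**5. Varying the patient-level SD as well.** Let s be the patient-level SD as a multiple of expected benefit. The planned probability is Φ((1 − c) / (s√(2/1,000))). With the effect sampled it is Φ((1 − c) / √(2s²/1,000 + 0.305²)).

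| c | s | As planned | Effect sampled |
|---|---|---|---|
| 0.8 | 1 | 1.00 | 0.74 |
| 0.8 | 3 | 0.93 | 0.73 |
| 0.8 | 5 | 0.81 | 0.70 |
| 0.9 | 1 | 0.99 | 0.63 |
| 0.9 | 3 | 0.77 | 0.62 |
| 0.9 | 5 | 0.67 | 0.60 |

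The planned value moves widely with s, which is a matter of simulation noise. The value with the effect sampled moves little with s. In every row the planned value lies further from 0.5.

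**The case against.** The strongest case on the other side has four parts.

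- **The text does not say the inputs are fixed.** Sections 12.3.1 and 12.3.2 name sources and do not say how values are entered. The model's handling of its own coefficients is left to cited publications. This stands, and it limits the point: no parameter sampling is stated. A reader might infer that sampling error in effects, costs and risk equations can never enter the analysis. The documents do not establish that. They do say first-order, so if second-order sampling is intended the text needs correcting.
- **The cohort size is fixed in advance.** It is tempting to argue that the analyst could push the probability to 0 or 1 by enlarging the cohort. That is true of the method in principle, but 14.2.4 sets 1,000 and leaves no such freedom.
- **The one-way analyses may vary the treatment effect.** They might, and a reader would then have something besides the curve. But they do not feed the curve, they cannot show joint uncertainty, and their parameters are not named. This softens the consequence without removing the problem.
- **The size is assumed.** No cost, QALY or patient-level variance is given, and independent draws between arms are an assumption. A large fall such as 0.87 to 0.58 needs a parameter SE five times the mean net benefit. This stands, which is why a range is shown.

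**Conclusion.** The point holds as a defect in the specification. The curve is built from first-order cohort means, and no section states any parameter sampling. Its spread is therefore simulation error that shrinks with the square root of the cohort size, and it does not represent decision uncertainty. The likely direction is overconfidence: under a normal model with the mean unchanged, any nonzero parameter SE pulls the probability towards 0.5.

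The size is uncertain. In the main illustration the planned 0.87 becomes anything from 0.86 to 0.58. This rests on assumed economic inputs and on a 30% relative SE for C-peptide that may not be the effect driving the model.

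Two stronger readings are not supported. A reader might conclude that the economic results would be meaningless, but the point estimates of incremental cost and QALYs are not the issue; what is wrong is reading the curve's probability as decision uncertainty. A reader might also take the 88 evaluable children (2 × 44) as the precision of the economic inputs, but that number belongs to the C-peptide sample size calculation. This is a secondary economic output, and the primary analysis is unaffected.

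**What to change.** In protocol 14.2.4, or in a health economics analysis plan that it refers to:

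- For each of the 1,000 runs, draw the treatment effects from the trial estimates with their covariance, or from a bootstrap of trial participants.
- In the same run, draw costs, utilities and, where the model allows, its coefficients from stated distributions.
- Build the scatterplot and acceptability curve from these second-order runs. Keep first-order runs only to check that Monte Carlo error is small.
- In 12.3.1, state which 12-month effects enter the model. In the sensitivity paragraph, name the parameters to be varied one at a time.

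The cost is protocol wording, computing time and a curve that looks less certain. No new data, visits or participants are needed.
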